### Aim and objectives

This 24-month research study initiative aims to engage a private provider network in select union councils of Islamabad Capital Authority (ICT) of Pakistan to improve access, uptake, and satisfaction and reduce OOP expenditure on quality OPD services at the primary health care level, including family planning and sexual and reproductive health services.

The specific objectives of this intervention are:

Examine and document the determinants of outpatient services access and uptake.Measure the changes in OOP expenditures, treatment outcomes, user satisfaction and quality of care.Study and document health insurance outcomes using the capitation model intervention for modified outpatient EPHS services.Generate evidence for the scale-up and delivery of integrated services as OPD services through SSP.*Users, providers, and policymakers’ perspectives will be examined and documented.

## Materials and methods

### Conceptual model

The proposed study’s conceptual model will have three components (i) the Theory of Change (Figure 1), (ii) the Logical Framework (Figure 2), and (iii) the Capitation-based Provider Payment Mechanism (PPM). The theory of change gives the big picture and summarizes work strategically, while a logic model will illustrate the program’s (implementation) level of understanding of the change process. In other words, the logic framework will use a microscopic lens that zooms in on a specific pathway within the theory of change. The capitation is a prospective payment unit per family (per month or year). A payer makes a fixed payment for a defined set of services, regardless of the number of services provided.

**Figure 1 fig1:**
[figure not shown]
The theory of change.

**Figure 2 fig2:**
[figure not shown]
The logical framework.

#### The theory of change

The assumption is that access to primary health care services will increase by deploying private general practitioners (GPs) in select areas where public sector-owned primary-level facilities are unavailable. Three components of the theory of change are (a) the Demand Side, (b) the Supply Side, and (c) Evidence generation.

The supply-side and demand-side components will be combined while health financing using capitation for PHC may create demand, thereby increasing the utilization of PHC services for the poorest of the poor outpatients. Evidence will be generated by documenting the extent to which the needs of the beneficiaries are met with quality, equitable, sustainable PHC service and if this has redefined health-seeking behavior at the community level. Evidence will also provide an understanding of the suitability of the intervention with possible recommendations for health financing and its scalability. Each component has a defined set of activities/interventions to achieve the desired output, immediate, intermediate, and ultimate outcomes (Figure 1). From an individual and household perspective, the ultimate outcome is designed to reduce out-of-pocket expenditure while increasing immunization status, contraceptive use, financial protection, and treatment effects among the enrolled beneficiaries (refer to Figure 1). While at the health facility level, this project emphasizes the delivery of quality health service by enhancing the clinical and counseling skills of health service providers, resulting in increased client flow and revenue for the self-suitability of the service delivery channels.

#### The logical framework

The proposed framework will describe the process of evaluating the quantitative outcomes of health care costs on families covered by health insurance schemes who receive OPD services (intervention arm) as compared to those covered under SSP but do not receive OPD services (control arm). Figure 2 summarizes inputs, processes, or outputs leading to intended outcomes.

The logical flow of the theory of change emphasizes the intermediate and immediate outcomes of improving the attitude toward health-seeking behavior of the beneficiaries based on the Information, Education and Communication (IEC) material and awareness about health services. While the capacity building of the service providers will increase client-centric communication, clinical monitoring, client exit interview surveys, and routine data gathering, its usage will ensure quality health service delivery and improvement. This intervention has been designed to address the financial barrier that restricts access to primary health care services. Hence, this project is expected to improve access and uptake, reduce out-of-pocket expenditure for quality outpatient health services at the PHC level, and produce evidence for recommendations and their scalability.

#### Capitation-based provider payment mechanism (PPM)

For this research study, a proposed capitation payment mechanism will be implemented as a test case within the country’s existing health systems due to the desire to contain the cost of care provision. Literature indicates that capitation is expected to promote efficient use of resources by controlling prices and volumes of services provided. Capitations have been used both as stand-alone or blended capitations in large parts of Europe, Thailand, South Korea etc. (44) which not only help in managing cost and serve as a critical source of income for the providers (45) but are also associated with increased adherence to policies and general guidelines on the part of providers (46). In this research study, recruited providers will receive a fixed payment to provide a pre-defined benefit package of EPHS to each enrolled family allocated to their facility over a fixed period of 12 months. The implementing partner (Marie Stopes, Pakistan) will disburse the provider capitation fee on a four (4) quarterly payment cycle.

To determine the best capitation mechanism, this study proposes to test and evaluate a quarterly capitation fee totaling PKR 2,900 (USD 17.55) (47) paid to service providers per family per year. The amount for capitation was decided based on essential services selected for the implementation of this research study. The essential services were derived from Pakistan’s UHC benefit package at the PHC level. Payment of capitation fees will be independent of service provision and will not depend upon all or a fraction of enrolled families utilizing the services.

### Study design

This research study will use a mixed method, two arms, prospective, quasi-experimental controlled before and after (CBA) design. The intervention group will include beneficiary families with existing in-patient coverage under SSP who will receive OPD services as part of the research study. In contrast, the control group includes families with existing inpatient coverage under SSP but will not receive OPD services.

#### Study area

The study will be conducted in four (4) union councils (UCs) of ICT of Pakistan. Intervention and control arms will be assigned based on UCs selected for the study. The following are criteria for UC identification: (1) UC with sufficient residents of existing SSP beneficiaries, (2) UC in rural classified areas of ICT, (3) UC in which there is no public sector PHC level facility such as a Basic Health Unit (BHU), and presence of a network of private sector managed registered General Practitioners (GPs) providing primary healthcare services within identified UCs.

#### Study population and sample size

The target population will be divided into (a) demand-side and (b) supply-side.

*Demand Side:* The total sample size for this study is 1726 beneficiary families (Baseline and end-line: control and intervention). This has been calculated by assuming the overall prevalence of health outcomes to be 50% (conventional) at baseline and an anticipated 10-percentage point change because of the intervention; with 80% power and 0.05 significance level, the total estimated sample was 388 for each study arm. The estimated sample was adjusted for a design effect 2 to account for facility-level clustering and 10% missing data / non-response. Hence an overall sample size of 863 families in the intervention- and 863 families in the control- group will be required to test the study objectives. Families in each study arm will be selected randomly from the available list of SSP beneficiary families from four peri-urban Union Councils of Islamabad Capital Territory (ICT). The intervention group (*N* = 863) will receive modified EPHS interventions as OPD services, while the Control group (*N* = 863) will not receive OPD services. Enrolled families in the intervention group will be informed about the project, and regular follow-up of SSP outpatient services accessed will be undertaken.

*Supply Side:* GPs who are members of Marie Stopes Pakistan’s primary healthcare franchise network will be selected based on their service provision status within the UCs identified for research study implementation. Individual and facility assessments will be done to ascertain the capacity to provide quality OP services to clients. A training curriculum will be jointly developed by the MoNHSRC, SSP, MSS, and WHO and will be used to train the selected GPs on the modified EPHS services. Periodic quality assurance visits and a centralized data-collection management information system will be implemented.

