### Quantitative household surveys

Before initiating the intervention, a household-based baseline survey is proposed that will cover not only the study population but also a subset of the general population from the same catchment who do not have the provision of any public or private sector health insurance. Findings will explore and explain health-related expenses and payment mechanisms if practiced or that exist other than the fee for service paid through OOP by clients in the study catchment area. The baseline survey will assess the prevalence of study indicators, document socio-economic and demographic information, out-of-pocket health expenditure, and document KAP regarding existing inpatient coverage and access and uptake of health services. A household-based endline survey at the end of 12 months of the intervention will help assess study outcomes – the impact of the outpatient services model on knowledge, attitude, and practice regarding health insurance, access, and uptake of outpatient services at the PHC level, user satisfaction, treatment outcomes, OOP health expenditure and financial protection.

Study participants for baseline and end-line assessment across the intervention and comparison arm will be selected randomly from the list frame of the SSP. Using quantitative and qualitative techniques, data collection methods will include a population-based household survey, providers’ assessment, and specific qualitative inquiry during the intervention, routine services, client satisfaction, and monitoring (clinical quality assessment) data will be done similarly to a previous study using the same design (50).

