#### Data analysis

The quantitative data analysis will focus on the combined effect of the complete package of interventions and the outcome(s) rather than exploring each component. Quantitative data will be analyzed through SPSS Software using descriptive and inferential statistics. The main outcome variables will be increased access, uptake, satisfaction, contraceptive prevalence, and reduction in OOP expenditure. Difference-in-differences (DiD) estimation will compare key outcome variables between the intervention and control group pre- and post-intervention (51). It will also measure the intervention effect on any subgroups in the intervention/control groups by comparing key outcome variables between beneficiaries in the intervention and control groups.

For the qualitative data, content and thematic analysis will be done in Nvivo Software version 11. Codes will be developed after reading the transcripts without losing the context. For qualitative analyses, transcripts will be read several times to understand the respondents’ in-depth experiences and views. ‘Meaning units’ that mirror statements will be identified as per the topic guide by highlighting phrases in the transcripts, which will be ‘condensed’, and after that ‘, codes’ will be identified from the ‘condensed meaning units’ without losing the context. Finally, the research team will review the codes independently and group similar codes into sub-categories and categories. From the categories, themes and sub-themes will be identified after systematically analyzing the commonalities, variations, and disagreements. We will further analyse data with a focus on the description and interpretation of message meaning and concepts to validate the study’s findings. Quantitative and qualitative data will be triangulated to provide comprehensive information about the impact of the research intervention. Figure 3 describes the components of the data synthesis plan envisaged for the project.

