
The validity is often compromised in quasi-experimental designs; however, our study will use statistical techniques and control measures to strengthen its validity, such as developing a study protocol as a standardized way to conduct the study to prevent researcher, instrumentation, or testing biases. When everyone follows the specific procedures, you can be more confident that the results will be valid. We will carefully select the control facility and justify the choice of the control group, ensuring that the control group is comparable to the intervention group in terms of relevant characteristics. A matched pre-post design would have been a stronger study design to compare behaviors of the same sample, as it will allow controlling for unobserved confounders such as to help address selection bias issues, control baseline differences and improve group comparability. Through Difference-in-Differences (DiD) analysis, we will compare outcome changes between the intervention and control groups, accounting for pre-existing trends. This will help control external factors that may affect both groups similarly. We will conduct validity checks for balance in covariates between groups before and after matching or weighting procedures. We will also provide clear and transparent reporting of methods, measures, and results to enhance the credibility and replicability of the study. In addition, respondents may have faced difficulties in answering questions or recall bias that captured information about their past experiences, such as information provided by the service provider about side effects at the time of method uptake, decision making and source of referral to the health facility or where the contraceptive method was adopted, exact time and discontinuation of method etc. Hence, whenever possible, we will try to supplement self-reported data with objective measures to validate the information provided by participants. Or to use standardized instruments and validated questionnaires to enhance the reliability of data collection.

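### The 80% power is calculated for one contrast of two proportions, while the planned estimator is a difference-in-differences, for which the documents give no between-wave correlation and so no support for 80%

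*Protocol article*

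**What the plan says.** The section *Study population and sample size* sets out the calculation by "assuming the overall prevalence of health outcomes to be 50% (conventional) at baseline and an anticipated 10-percentage point change because of the intervention". It then reports that "with 80% power and 0.05 significance level, the total estimated sample was 388 for each study arm". Two inflations follow, each with a named purpose: "The estimated sample was adjusted for a design effect 2 to account for facility-level clustering and 10% missing data / non-response". The result is "863 families in the intervention- and 863 families in the control- group".

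The section *Data analysis* names the estimator: "Difference-in-differences (DiD) estimation will compare key outcome variables between the intervention and control group pre- and post-intervention". *Possible limitations and strengths* repeats that DiD is the basis of comparison.

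The article points both ways on whether the same families are measured twice:

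- *Quantitative household surveys* says that participants for both assessments "will be selected randomly from the list frame of the SSP".
- *Possible limitations and strengths* says that "A matched pre-post design would have been a stronger study design to compare behaviors of the same sample", which reads as though that design was not adopted.
- *Inclusion and exclusion criteria* confines the endline to beneficiaries already enrolled in the study and leaves out those who refused or moved away. That is cohort language.

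**The concern.** A DiD contrasts four cell means (two arms at two waves), and the calculation uses two proportions. Sampling error in the other two cells is not allowed for. Both inflations are already assigned, one to facility clustering and one to non-response, so no allowance for a second wave is hidden in 863.

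Unless the two waves are substantially correlated, the study has less than its stated power for the analysis it plans. A null DiD could then be read as evidence against a 10-point effect when the study was not well placed to detect one. That matters because one of the stated objectives is to generate evidence for scale-up.

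**Working it through.** **Inputs from the article.** 50% at baseline, a 10-point change, 80% power, alpha 0.05, design effect 2, 10% loss, 863 per arm. Sidedness is not stated; two-sided reproduces the figure.

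**1. The plan's own figure.** Two-sided pooled formula for 0.50 against 0.60:

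n = [1.96 × √(2 × 0.55 × 0.45) + 0.8416 × √(0.25 + 0.24)]² / 0.10² = 387.3, rounded up to 388.

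388 × 2 = 776, and 776 / 0.9 = 862.2, rounded up to 863. Every step reproduces. Power at 388 per arm is 80.1%.

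**2. Effective size per arm per wave.** 863 × 0.9 / 2 = 388.

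**3. The DiD.** Control stays at 0.50 and intervention goes from 0.50 to 0.60. The four variances sum to 0.25 + 0.25 + 0.25 + 0.24 = 0.99, so with correlation r between baseline and endline arm means:

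Var(DiD) ≈ 0.99 × (1 − r) / 388.

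The single contrast has variance 0.49 / 388. The ratio is 0.99(1 − r) / 0.49, or about 2(1 − r). Power = Φ(0.10 / SE − 1.96).

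| r | SE | Power |
|---|---|---|
| 0 | 0.0505 | 51% |
| 0.1 | 0.0479 | 55% |
| 0.2 | 0.0452 | 60% |
| 0.3 | 0.0423 | 66% |
| 0.4 | 0.0391 | 72% |
| 0.5 | 0.0357 | 80% |
| 0.6 | 0.0320 | 88% |

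At r = 0 the detectable difference at 80% power is (1.96 + 0.8416) × 0.0505 = 0.1415, about 14 points.

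**4. Where r can come from.** A design effect of 2 for facility clustering means that half of each cell's variance is the facility component and half the family component. Let c be the baseline-endline correlation of facility effects and w the within-family correlation net of facility, with w = 0 if different families are surveyed. Then r = (c + w) / 2. Neither c nor w is in the documents; these values are assumptions that show the range.

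- Different families (w = 0), c = 0.5: r = 0.25, SE = √(0.99 × 0.75 / 388) = 0.0437, power about 63%.
- Different families, c = 0.8: r = 0.4, power about 72%.
- Different families, c = 1: r = 0.5, power about 80%.
- Same families, c = 0.8 and w = 0.2: r = 0.5, power about 80%.

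**The case against.** The strongest reply is that separate samples of families do not make the waves independent. The design effect is for facility clustering, and both waves cover the same intervention and control areas. Stable facility effects cancel in a DiD even when the families differ. This stands. A reader might infer that the study has 51% power, or that 80% is reached only if the same families are re-interviewed with a within-family correlation of at least 0.5. The documents support neither. The 51% needs facility effects to be wholly uncorrelated between waves about a year apart, so it is the low end of a range. Step 4 shows that facility stability and family repetition contribute to r together.

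It can also be said that the cohort reading is at least as well supported. The endline is limited to enrolled beneficiaries, the outpatient package goes to the 863 enrolled intervention families, and *Ethics and dissemination* gives each participant one identifier for all forms. That is fair, but two other sections point the other way. Under the cohort reading, power still depends on an r that is never stated.

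Two further inferences go beyond the text. The calculation is not identified as an endline comparison between arms: 50% at baseline and a 10-point change could equally be a before-after contrast in one arm. Either way it is not a DiD. And although "The total sample size for this study is 1726 beneficiary families (Baseline and end-line: control and intervention" could suggest that the total is divided between waves (which would leave 194 effective per cell and about 29% power at r = 0), the article treats 863 as the size of each group, so that reading is not adopted here.

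**Conclusion.** The point holds as a mismatch between the power statement and the estimator. The arithmetic behind 388 and 863 is correct for what it computes. What it computes is not the planned DiD, so 80% power is not shown for the planned analysis.

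Power for a 10-point DiD starts at about 51% and reaches 80% only when r is about 0.5 or more. This rests on 863 families per arm at each wave, the plan's own design effect of 2 and 10% loss, a two-sided 5% test and the normal approximation. The documents do not show that the study is underpowered, because r is unknown. They do not support an unqualified 80% either, whether the waves are a panel or separate samples.

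This is not a detail left to a fuller plan: the article states both the power and the estimator, and they do not match.

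**What to change.** 1. Reconcile *Inclusion and exclusion criteria* (endline on enrolled families) with *Quantitative household surveys* and *Possible limitations and strengths* (random selection from the list for both assessments; a same-sample design described as the stronger alternative). State whether the design is a panel or repeated cross-sections.
2. Restate power for the DiD. Possible wording: *With 863 families per arm at each wave, a design effect of 2 and 10% loss, power for a 10-point difference-in-differences is about 51%, 66% and 80% for baseline-endline correlations of the arm means of 0, 0.3 and 0.5; with no correlation the detectable difference at 80% power is about 14 points.* Alternatively, give one value under a correlation justified from data, counting both facility stability and any repeated families.
3. If the same families are re-interviewed, link the waves by the study identifier and analyse within-family change, with facility clustering accounted for, so that the correlation is used.

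No extra families are requested. The cost is a revised sample-size paragraph, consistent wording on sampling, and a less favourable stated power.

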**Methods and analysis:**

A 24-month research study is proposed with a 12-month intervention period using a mixed method, two-arm, prospective, quasi-experimental controlled before and after design with a sample of 863 beneficiary families from each study arm, i.e., intervention and control groups (*N* = 1726) will be selected through randomization at the selected beneficiary family/household level from four peri-urban Union Councils of ICT where no public sector PHC-level facility exists. All ethical considerations will be assured, along with quality assurance strategies. Quantitative pre/post surveys and third-party monitoring are proposed to measure the intervention outcomes. Qualitative inquiry with beneficiaries, general practitioners and policymakers will assess their knowledge and practices.

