#### Inclusion and exclusion criteria

Families with existing in-patient coverage of SSP, having SSP cards, and currently residing within the intervention or control areas of selected UCs of ICT will be considered eligible for inclusion in the research study and the baseline survey. Families not yet registered as beneficiaries with SSP and married children of SSP card holders were excluded. The endline survey will also follow similar inclusion–exclusion criteria as the baseline, i.e., to be conducted on those beneficiaries who were enrolled for the research study in the intervention and control UCs and those who were refusals or migrated cases will be excluded from the endline survey. The eligibility of each beneficiary family will be re-verified before inclusion through the National Database and Registration Authority (NADRA) website and by sending a Computerized National Identity Card (CNIC) number to 8,500 via short message service (SMS).

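### Arms are assigned by union council with only four councils, but the sample size allows only for facility-level clustering, so the stated 80% power is conditional on negligible council-level variation in change over time

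*Protocol article*

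**What the plan says.** The Study area section fixes both the number of areas and the level of assignment: "The study will be conducted in four (4) union councils (UCs) of ICT of Pakistan", and "Intervention and control arms will be assigned based on UCs selected for the study". The eligibility criteria agree, since families must be "currently residing within the intervention or control areas of selected UCs of ICT". The split of the four councils between arms is not given.

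The Study population and sample size section starts from a comparison of two proportions, "assuming the overall prevalence of health outcomes to be 50% (conventional) at baseline and an anticipated 10-percentage point change because of the intervention", and reports that "with 80% power and 0.05 significance level, the total estimated sample was 388 for each study arm". It continues: "The estimated sample was adjusted for a design effect 2 to account for facility-level clustering and 10% missing data / non-response". The result is that "an overall sample size of 863 families in the intervention- and 863 families in the control- group will be required". No allowance for variation between councils is described.

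The Data analysis section plans a difference-in-differences comparison of the arms. The Possible limitations and strengths section acknowledges non-random assignment, convenience choice of facilities, area differences and competing providers. It does not mention the small number of assigned areas. It also anticipates that any rise in outcomes can be put down to the intervention.

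**The concern.** Whether a family is offered the intervention depends on the council it lives in. Anything that makes outcomes move differently from one council to another over the 12 months (local prices, a provider opening or closing, a local shock) is therefore mixed with the intervention effect. It is averaged out only over the number of councils, which is four. Sampling more families within a council does not reduce it.

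The design effect of 2 is attributed to facilities, a level below the one at which arms are assigned. Whether it also covers council-level variation is an unstated assumption, yet the 80% is given without qualification. The study is meant to inform scale-up of outpatient cover, so readers may credit the result with more precision than four areas can provide.

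**Working it through.** **Inputs from the protocol.** 50% and 60%; alpha 0.05; power 80%; design effect 2; 10% non-response; four councils. **Assumed, because the article gives no figure:** two councils per arm, a two-sided test, and a range of ICCs.

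**Step 1: reproduce the plan's figure.** Pooled-variance formula without continuity correction:

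n = [1.960 × √(2 × 0.55 × 0.45) + 0.842 × √(0.5 × 0.5 + 0.6 × 0.4)]² / 0.10² = (1.379 + 0.589)² / 0.01 = 387.3, rounded up to 388.

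388 × 2 = 776; 776 / 0.9 = 862.2, rounded up to 863. Both figures match, so there is no arithmetic error.

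**Step 2: what a design effect of 2 means at council level.** Analysed families per council: 776 / 2 = 388. From design effect = 1 + (m − 1) × ICC with m = 388, a value of 2 gives ICC = 1 / 387 = 0.0026.

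**Step 3: power over a range of council-level ICCs.** The effective sample per arm is 776 / design effect. The normal-reference column puts it into the Step 1 formula. The other column uses a noncentral t with 4 − 2 = 2 degrees of freedom (critical value 4.30) and noncentrality 0.10 / √(0.49 / effective n). At design effect 2 the noncentrality is 0.10 / √(0.49 / 388) = 2.81.

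| ICC | Design effect | Effective n per arm | Power, normal | Power, t with 2 df |
|---|---|---|---|---|
| 0 | 1.00 | 776 | 98% | 56% |
| 0.001 | 1.39 | 560 | 92% | 46% |
| 0.0026 | 2.00 | 388 | 80% | 35% |
| 0.005 | 2.94 | 264 | 64% | 27% |
| 0.01 | 4.87 | 159 | 43% | 19% |
| 0.02 | 8.74 | 89 | 27% | 13% |

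**Step 4: how this carries over to the planned DiD.** The table is for a single-wave contrast. DiD removes stable differences between councils, so the ICC that matters is the council-by-period component, which may be smaller than a cross-sectional ICC. The variance is also multiplied by 2(1 − r), where r is the correlation between waves. Hold the effective sample at 388 per arm in each wave, use a variance term of 0.49 in both waves, and take a normal reference. Power is then 51% at r = 0, 66% at r = 0.3, 80% at r = 0.5 and 95% at r = 0.7. The single-wave figures can therefore err in either direction for the DiD. A council-level analysis of change still has 2 degrees of freedom.

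**The case against.** The best defence has four parts.

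- **The plan does not ignore clustering.** It halves the effective sample, and the facility level is a sensible choice because families are allocated to facilities and capitation is paid to providers. This stands. A reader might infer that the plan treats families as independent, and the design effect shows that it does not.
- **The ICCs and the 2:2 split are not in the protocol.** This also stands. A reader might infer that the 80% is simply false. The documents do not support that: with a normal reference it holds if council-level variation is small enough. What they support is that the condition is unstated and unsupported.
- **A test on council means with 2 degrees of freedom is not the planned analysis**, and by that standard even ICC 0 gives only 56%. True. The 2-df column shows how little information four assigned areas carry; it does not forecast the planned test. Nor should a reader argue from the few ways of permuting four councils between arms. The protocol plans no such test and claims no random allocation of councils.
- **DiD removes area differences.** It removes stable ones only. Differential change between councils remains.

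The abstract could be read as pointing to family-level allocation, since families "will be selected through randomization at the selected beneficiary family/household level from four peri-urban Union Councils of ICT". Beside the Study area section and the eligibility criteria, this reads as random selection of families within areas already assigned to an arm.

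How standard errors will be clustered, and how the design effect was derived, may be in a fuller document. Their absence from the article is not held against it. The point concerns what the article does fix: the level of assignment, the number of areas, the level of the clustering allowance and an unqualified power.

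**Conclusion.** The point holds in conditional form. Arms are assigned by council, there are four councils, and the sample size makes a stated allowance only for facility-level clustering. The 80% power therefore depends on negligible council-level variation in change over time.

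On size, a design effect of 2 covers a council-level ICC of only about 0.0026. At 0.01 and 0.02, single-wave power falls to about 43% and 27%. A council-level analysis would have about 35% at design effect 2 and no more than about 56% with this sample. These percentages rest on two councils per arm, 776 analysed families per arm and assumed ICCs. They are not estimates of power for the planned DiD, which depends on the council-by-period component and on the wave correlation, neither of which the article gives. It is also unclear how far the same families are surveyed twice. The eligibility section says the endline covers enrolled beneficiaries, while the household survey section describes random selection for both waves and the limitations section treats a matched design as one not adopted.

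The structural point is firm; the percentages are illustrative.

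**What to change.** In the Study population and sample size section, replace the unqualified 80% by one of two statements:

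- power computed with the union council as the unit of assignment, over a stated range of ICCs and with a stated assumption about the correlation between waves; or
- a sentence saying that 80% holds only if council-by-time variation is negligible.

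Report baseline-to-endline change for each of the four councils beside the pooled DiD estimate. Limit the conclusion to a comparison of four communities, and qualify the sentence in Possible limitations and strengths that credits any increase to the intervention.

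The cost is a less favourable stated power, some rewording and one extra table. Sample size and fieldwork do not change.
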